## 7. Staff involved in the management or conduct of this study

Individuals with tendonitis, carpal tunnel syndrome, or other musculoskeletal disorders should consult their doctor prior to using the Ava bracelet.

When the informed consent is provided in the portal (see sections 8 and 11), some baseline questions will be asked after which the subject will be randomized and receive the starter kit (Section 8.4.6).

### 4.4 Sample size calculation

A crossover design will be used in the current study meaning that subjects will contribute data to both the control and experimental condition. Unlike a traditional crossover study, however, the proposed crossover design includes a missing-data mechanism by design. Subjects with SARS-CoV-2 infection in the Learning Phase will have their data excluded from Period 1 and Period 2. Likewise, subjects with SARS-CoV-2 infection in Period 1 will have their data excluded from Period 2. This prevents the application of standard statistical adjustments due to missing-data. A bootstrap approach will be used to conduct statistical testing which accounts for this missing data mechanism in those cases when both periods are taken into account in the analysis. For more details, refer to Section 10 (Statistical analysis). With analyses based on bootstrap methods, classical power calculations are not possible. However, we can gain an indication of the bounds on power that can be expected. Additionally, power is highly dependent on the infection rate in the Netherlands during the conduct of the trial and for which we expect continued volatility, therefore we present power approximations based on the data reported by the RIVM on the number of individuals tested and found positive for SARS-CoV-2 infection in Weeks 36 through 40 of 2020, see Table 2.

*Table 2: Number of individuals tested in the Netherlands and amount of positive tests as reported by RIVM in Weeks 36 through 40 of 2020*

|                           | Week 36 | Week 37 | Week 38 | Week 39 | Week 40 |
|---------------------------|---------|---------|---------|---------|---------|
| Individuals Tested | 180,182 | 191,204 | 206,670 | 207,670 | 223,274 |
| Positive tests     | 5,427   | 7,640   | 12,217  | 16,602  | 23,264  |

#### 4.4.1 Ever-infected analysis

For the first analysis that will be performed for the primary analysis, log-linear modelling will be used. As an approximation, we will use the power calculation of a Fisher exact test. We provide power estimates based upon 10,000 subjects per arm as will approximately be

available within Period 2. In Table 3 and Table 4 both scenarios are presented given different assumed infection rates in the Netherlands and for various differences in sensitivity (Table 3) and specificity (Table 4) to be detected. From these assessments of the trial power, we see that the most recent RIVM data lead to sufficient power for differences in sensitivity of at least 5.5%. We also see that the trial is well powered for very small changes in specificity with sufficient power for differences of at least 1.5%.

*Table 3: Trial power for a Fisher exact test to detect differences in sensitivity based on infections rates of Weeks 36 through 40 of 2020*

|                                | Week 36 | Week 37 | Week 38 | Week 39 | Week 40 |
|--------------------------------|---------|---------|---------|---------|---------|
|                                | 10,000  | 10,000  | 10,000  | 10,000  | 10,000  |
| Difference in Sensitivity 1%   | 0.03    | 0.03    | 0.04    | 0.04    | 0.05    |
| Difference in Sensitivity 2.5% | 0.03    | 0.05    | 0.07    | 0.09    | 0.13    |
| Difference in Sensitivity 4%   | 0.06    | 0.1     | 0.16    | 0.23    | 0.33    |
| Difference in Sensitivity 5.5% | 0.1     | 0.18    | 0.31    | 0.45    | 0.62    |
| Difference in Sensitivity 7%   | 0.18    | 0.32    | 0.55    | 0.72    | 0.88    |

Table 4: Trial power for a Fisher exact test to detect differences in sensitivity based on infection rates of Weeks 36 through 40 of 2020

|                                 | Week 36 | Week 37 | Week 38 | Week 39 | Week 40 |
|---------------------------------|---------|---------|---------|---------|---------|
|                                 | 10,000  | 10,000  | 10,000  | 10,000  | 10,000  |
| Difference in Specificity -3%   | 1       | 1       | 1       | 1       | 1       |
| Difference in Specificity -1.5% | 0.79    | 0.78    | 0.75    | 0.76    | 0.73    |
| Difference in Specificity 1.5%  | 0.82    | 0.79    | 0.77    | 0.76    | 0.76    |
| Difference in Specificity 3%    | 1       | 1       | 1       | 1       | 1       |

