It is currently thought that most – but not all - infected individuals develop symptoms, but that the infectious period starts on average two days before the first overt symptoms appear (2). It is estimated that pre- and asymptomatic individuals are responsible for up to half of all transmissions (3,4). Studies on COVID-19 reported that fever (87.9% of cases), dry cough (67.7% of cases), and shortness of breath (18.6% of cases) are the most frequent presenting symptoms (5–8). Close to half (44%) of infected Chinese patients reported to treatment centres with fever as their first presenting symptom (9). While not specific to COVID-19, body temperature and pulse rate increase during fever (10,11) and shortness of breath can be measured by increased breathing rate. A recent paper examining the validity of wrist temperatures compared to forehead and tympanic temperatures among Chinese COVID-19 patients found less overall variability in wrist temperatures (10). Increases in temperature, pulse rate, and breathing rate could therefore be early signs of a SARS-CoV-2 infection, especially if exposure to SARS-CoV-2 is known to have occurred (10). By detecting infected

individuals before they have overt symptoms, the proportion of transmissions by presymptomatic individuals could potentially be significantly reduced. As of December 2020, the first of several vaccines developed specifically for COVID-19 have been approved by regulatory authorities. Like many other countries, the government of the Netherlands is aiming to vaccinate the large majority of the Dutch population by the end of 2021. Given the differences in effectiveness between manufactured vaccines, the uncertainties surrounding the duration of protection afforded by these vaccines, as well as the difficulty in vaccinating a large majority of the population in a timely manner, the (early) detection of COVID-19 in both unvaccinated and vaccinated individuals remains a crucial component to contain the pandemic. As such, vaccinated individuals will be eligible to participate in this study and those vaccinated during follow-up will remain in the study to contribute valuable data.

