### 3.3 Implementation and development of algorithms

For both the control and experimental conditions, separate algorithms will be applied. For the control condition, an algorithm meant to predict potential active SARS-CoV-2 infections will be applied that incorporates deterministic expert-based rules regarding the presence of SARS-CoV-2 symptoms defined by the Dutch national institute for public health and the environment ‘Rijksinstituut voor Volksgezondheid en Milieu’ (RIVM) guidelines (at the time of writing these include: common cold symptoms [such as a nasal congestion, runny nose, sneezing, sore throat], coughing, shortness of breath, elevated temperature or fever, and sudden loss of smell and/or taste [without nasal congestion]). Any subject that experiences any of the above symptoms will be advised to get tested. For the experimental condition, a machine learning algorithm developed for the same purpose based on both symptom and confounder data as well as physiological parameters collected through the Ava bracelet will be applied on data collected during the study from the Daily Symptom Diary and the Ava bracelet. Both algorithms will give recommendations to the subjects whether they should get tested for SARS-CoV-2 infection. For the algorithm in the experimental condition to give a recommendation based on physiological data, it is first required to establish a baseline per subject of their “normal” physiological patterns. The period of time in which this baseline is determined is referred to as “baselining”. This will take place when subjects enter the study and will not be repeated within each period of the crossover portion of the trial. As soon as a stable baseline has been determined for all measured physiological parameters, the algorithm can start detecting when there are significant deviations from this baseline. For the

remainder of the Learning Phase the experimental condition algorithm will be applied for subjects that are part of this Phase. In Period 1 and 2, data from only the Daily Symptom Diary (control condition) or both the Diary and the bracelet (experimental condition) will be used to inform the algorithms that give indications to the subjects whether they should seek testing.

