#### 4.4.2 Early detection analysis

The second statistical analysis that will be performed for the primary objective concerns the timing of each study condition to detect SARS-CoV-2. The time to first SARS-CoV-2 indication or infection will thus be compared between the conditions. This will be tested using a stratified log-rank test. Frequently, power calculations for the log-rank test assume some form of proportional hazards or a specific parametric family for the study arms. In this study, we expect the experimental condition to be able to detect SARS-CoV-2 infection earlier due to the possible detection of pre- or asymptomatic individuals due to deviations in physiological parameters. However, when subjects become symptomatic, the algorithms in both the control and experimental condition will each declare subjects to likely be infected at the same moment by definition. To account for this aspect, a piecewise log-rank test power calculation is used to characterize the trial power. The assumption in the piece-wise hazards is that initially the experimental condition will have a higher chance to detect SARS-CoV-2 infection; however, this difference will decrease over time resulting in equal hazards in the later pieces of the hazard function. As described in the first analysis above, the proposed crossover design results in an application of bootstrap statistical testing so that the power calculations in Table 5 are rough approximations. The estimated power is bounded below by a parallel-arm study with 10,000 subjects per condition and above by a study with 20,000 subjects per condition. From these bounds it appears that the trial is well powered under all of the recently reported RIVM data.

Table 5: Lower (10,000) and upper (20,000 ) bounds of the trial power for a piecewise log-rank test to detect differences between study conditions on the time to first SARS-CoV-2 indication or infection based on infection rates of Weeks 36 through 40 of 2020

|              | Week 36 |      | Week 37 |      | Week 38 |      | Week 39 |      | Week 40 |      |
|--------------|---------|------|---------|------|---------|------|---------|------|---------|------|
|              | 10k     | 20k  | 10k     | 20k  | 10k     | 20k  | 10k     | 20k  | 10k     | 20k  |
| Power | 0.66    | 0.92 | 0.80    | 0.98 | 0.94    | 0.99 | 0.99    | 1.00 | 1.00    | 1.00 |

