### *General statistical approach*

Appropriate statistical methods will be selected for each research question depending upon the nature of the data distribution as well as the effect that is to be characterized. Categorical variables will be presented as absolute numbers and percentages, while continuous variables will be described by number of observations, mean, standard deviation, median and range (minimum and maximum). While maximum effort will be put into the minimization of missing data, the remote nature of the study and the reliance on self-reporting by the subjects might lead to the presence of missing data. Where necessary, missing data mechanisms will be investigated and imputation methods will be used or robust statistical methods such as bootstrap estimation employed. The count and percentage of known missing data will be described. Analyses and results between and within the study conditions will also be reported overall and separately for the different strata (e.g., normal-risk vs. high-risk population). Additionally, with the exception of the baseline data, all data will be analysed and reported within each period of the trial with pooling of the data only in specifically mentioned cases in the sections below. All statistical confidence intervals will be two-sided and at the 95% level. P-values, or similar measures resulting from bootstrap methods, will be considered significant if less than 0.05 with two-sided testing and if less than 0.025 with one-sided testing. No adjustments for multiplicity of tests are planned. For both the primary and secondary endpoints (where relevant), we will assess the COVID-19 vaccinated portion of the study sample as a key subset. The potential effect of COVID-19 vaccination among some subjects on the analyses of interest will be investigated using sensitivity analyses. This may include truncation of certain data occurring after vaccination events as part of these sensitivity analyses. Further details will be captured in the statistical analysis plan.

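### Section 4.4.1 calls power sufficient for sensitivity differences of 5.5 points or more, but Table 3's best 5.5-point cell is 0.62, and even that appears to rest on an unstated and favourable control sensitivity of 0.90

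*Protocol*

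**What the plan says.** Section 4.4.1 plans log-linear modelling for the ever-infected comparison and substitutes a simpler test for power: "As an approximation, we will use the power calculation of a Fisher exact test". On size it says: "We provide power estimates based upon 10,000 subjects per arm". Results are shown "given different assumed infection rates in the Netherlands and for various differences in sensitivity (Table 3) and specificity (Table 4) to be detected". The rows of Table 3 are differences in sensitivity (1, 2.5, 4, 5.5 and 7 points) and the columns are Weeks 36 to 40. The text concludes that, on the most recent RIVM data, power is sufficient from a 5.5-point difference upward.

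Two inputs that such a calculation needs are absent: the sensitivity of the control algorithm and the number of infected subjects per arm.

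The control algorithm (section 3.3) is a deterministic rule on RIVM symptoms: "Any subject that experiences any of the above symptoms will be advised to get tested". The reference standard (section 10.2) counts a subject as infected after a positive virus test in Period 2 or a positive serology result at its end. The introduction says: "It is currently thought that most – but not all - infected individuals develop symptoms".

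**The concern.** There are two problems, one on the face of the table and one behind it.

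First, the summary sentence does not match the table. Anyone who relies on the sentence will think a 5.5-point gain in sensitivity is detectable with adequate power, when the largest printed value is 0.62.

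Second, power for a fixed difference between two proportions depends strongly on where the proportions lie, and is greatest near 0 or 1. Without the control sensitivity and the infected count, the table cannot be checked or carried over to other conditions. If the hidden control sensitivity is optimistic, every entry is optimistic, and a null result on sensitivity, which is part of the primary analysis, could be read as evidence that the bracelet adds nothing.

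**Working it through.** **1. The sentence against the table.** The most recent data are Week 40.

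| Difference | Wk 36 | Wk 37 | Wk 38 | Wk 39 | Wk 40 |
|---|---|---|---|---|---|
| 5.5 points (printed) | 0.10 | 0.18 | 0.31 | 0.45 | 0.62 |
| 7 points (printed) | 0.18 | 0.32 | 0.55 | 0.72 | 0.88 |

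The protocol sets no power target. Against the usual 0.80, only one of 25 cells passes. The protocol's own usage is no kinder: for specificity it calls 1.5 points sufficient on Table 4 cells of 0.73 to 0.82, and 0.62 lies below all of these.

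**2. Recovering the unstated inputs.** Stated inputs: Fisher exact test and 10,000 per arm (section 4.4.1); level, "will be considered significant if less than 0.05 with two-sided testing" (section 10); weekly positive tests from Table 2, "5,427 | 7,640 | 12,217 | 16,602 | 23,264".

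Power is the sum of Bin(x₁; n, p) × Bin(x₂; n, p + d) over all pairs (x₁, x₂) with two-sided Fisher p-value at or below 0.05. Here n is the number infected per arm, p the control sensitivity and d the difference.

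*Try n = positivity × 10,000.* For Week 40, 23,264 / 223,274 × 10,000 = 1,042; over the five weeks n = 301, 400, 591, 799, 1,042. The 7-point row is then 0.38, 0.49, 0.66, 0.78, 0.89 at p = 0.50 and 0.93, 0.98, 1.00, 1.00, 1.00 at p = 0.90. No control sensitivity tried (0.50 to 0.92) reproduces the printed row.

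*Try n proportional to positive tests.* With 250 at Week 40, Week 36 has 250 × 5,427 / 23,264 = 58; over the five weeks n = 58, 82, 131, 178, 250. At p = 0.90:

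| Difference | Computed, Wk 36 to 40 | Printed |
|---|---|---|
| 5.5 points | 0.10, 0.18, 0.31, 0.44, 0.61 | 0.10, 0.18, 0.31, 0.45, 0.62 |
| 7 points | 0.18, 0.32, 0.55, 0.72, 0.88 | 0.18, 0.32, 0.55, 0.72, 0.88 |

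All 25 cells agree within about 0.01. Week 40 counts from 245 to 256 keep every cell within 0.02.

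*How well is 0.90 pinned down?* With n proportional to positive tests and scaled to match the 0.88 cell, the cells within 0.02 number 25 at p = 0.90, 18 at 0.89, 17 at 0.91, 7 at 0.85 and 6 at 0.80. With n free to vary by week, the largest miss is 0.011 at p = 0.90, 0.025 at 0.85, 0.051 at 0.80 and 0.121 at 0.60.

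**3. What 0.90 implies.** Section 4.4.2 says both algorithms flag a subject at the same moment once symptoms appear. On that logic, a gain in ever-detected infections must come from those the symptom rule misses. Going from 0.90 to 0.97 means finding (0.97 − 0.90) / (1 − 0.90) = 70% of them.

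**4. Sensitivity of the best cell.** Power at Week 40 with n = 250:

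| Control sensitivity | 7 points | 5.5 points |
|---|---|---|
| 0.90 | 0.88 | 0.61 (printed 0.62) |
| 0.85 | 0.65 | 0.42 |
| 0.80 | 0.52 | 0.33 |
| 0.70 | 0.39 | 0.25 |
| 0.60 | 0.33 | 0.22 |

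The infected count matters as much. At control sensitivity 0.80, 7-point power is 0.52 with 250 infected per arm, 0.73 with 400, 0.89 with 600 and 0.99 with 1,042. At 0.60 it rises from 0.33 with 250 to 0.91 with 1,042.

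**The case against.** **No cell is miscalculated.** The table is reproduced, section 4.4 offers only approximations and warns that power depends heavily on the infection rate, and most printed values are openly low. This stands. The error is in the summary sentence; the rest concerns undisclosed inputs.

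**The documents do not rule out 0.90.** They give no asymptomatic share. The control rule fires on any common-cold symptom, and one red light at any time in three months counts as detection. This also stands: the wide reference standard creates a tension with 0.90, not a contradiction. Chance alarms explain little of it, though. Table 4 fits a specificity of about 0.80 to 0.83. If infected subjects had unrelated red lights at the matching 17%, true detection would still have to be (0.90 − 0.17) / 0.83 = 0.88. The intention-to-treat set also includes subjects with incomplete diaries, and an unlogged symptom cannot trigger the rule.

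**The range 0.60 to 0.80 is an assumption.** So it is, and the powers quoted for it also hold the inferred 250 infected per arm fixed.

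**A stronger reading that fails.** A reader might infer that Table 5 contradicts Table 3. With the same counts and every infection taken as an event, Table 5 corresponds to a constant hazard ratio near 1.55, whereas a control that detects 90% can be exceeded by a factor of at most 1/0.90 = 1.11. From that one might conclude that control sensitivity must be about 65% or less. But a hazard ratio measures speed and is not capped by the final proportion detected. Section 4.4.2 is about timing: "we expect the experimental condition to be able to detect SARS-CoV-2 infection earlier due to the possible detection of pre- or asymptomatic individuals". On a time-since-infection scale with control reaching 90%, a ratio of 1.55 gives 1 − 0.10^1.55 = 0.97, which is Table 3's 7-point row. A log-rank simulation on that basis gave 0.61, 0.77, 0.94, 0.98 and 1.00, against the printed 0.66, 0.80, 0.94, 0.99 and 1.00. Table 5's hazards, event counts and time axis are unstated, so no conflict is shown.

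**Conclusion.** The conclusion in section 4.4.1 is wrong on the protocol's own figures: 5.5 points reaches at most 0.62, and only 7 points at the Week 40 rate (0.88) exceeds 0.80. This needs no assumption beyond the conventional benchmark.

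That Table 3 rests on control sensitivity 0.90 with roughly 58 to 250 infected per arm is an inference from fit, but a tight one. The 0.90 is favourable and unjustified in the text. A fall of five points, to 0.85, takes the best cell from 0.88 to 0.65; an assumed 0.60 to 0.80 takes it to 0.33 to 0.52. These figures hold for 250 infected per arm. The documents do not show that 0.90 is impossible, nor that the comparison would be underpowered at a higher infection count.

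**What to change.** In section 4.4.1:

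- Replace the conclusion about 5.5 points with what Table 3 supports: about 7 points, at the Week 40 rate only.
- State the control sensitivity and the number infected per arm for each week, how that number follows from Table 2, and why the control value is reasonable for a symptom-only rule judged against virus testing plus serology.
- Show power over a range of both inputs, for example control sensitivity 0.60 to 0.90 and several infected counts.

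The cost is recalculation and rewording. Enrolment, conduct and the planned analysis are unchanged. The drawback is that the stated power becomes less favourable.

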#### 4.4.2 Early detection analysis

The second statistical analysis that will be performed for the primary objective concerns the timing of each study condition to detect SARS-CoV-2. The time to first SARS-CoV-2 indication or infection will thus be compared between the conditions. This will be tested using a stratified log-rank test. Frequently, power calculations for the log-rank test assume some form of proportional hazards or a specific parametric family for the study arms. In this study, we expect the experimental condition to be able to detect SARS-CoV-2 infection earlier due to the possible detection of pre- or asymptomatic individuals due to deviations in physiological parameters. However, when subjects become symptomatic, the algorithms in both the control and experimental condition will each declare subjects to likely be infected at the same moment by definition. To account for this aspect, a piecewise log-rank test power calculation is used to characterize the trial power. The assumption in the piece-wise hazards is that initially the experimental condition will have a higher chance to detect SARS-CoV-2 infection; however, this difference will decrease over time resulting in equal hazards in the later pieces of the hazard function. As described in the first analysis above, the proposed crossover design results in an application of bootstrap statistical testing so that the power calculations in Table 5 are rough approximations. The estimated power is bounded below by a parallel-arm study with 10,000 subjects per condition and above by a study with 20,000 subjects per condition. From these bounds it appears that the trial is well powered under all of the recently reported RIVM data.

Table 5: Lower (10,000) and upper (20,000 ) bounds of the trial power for a piecewise log-rank test to detect differences between study conditions on the time to first SARS-CoV-2 indication or infection based on infection rates of Weeks 36 through 40 of 2020

|              | Week 36 |      | Week 37 |      | Week 38 |      | Week 39 |      | Week 40 |      |
|--------------|---------|------|---------|------|---------|------|---------|------|---------|------|
|              | 10k     | 20k  | 10k     | 20k  | 10k     | 20k  | 10k     | 20k  | 10k     | 20k  |
| Power | 0.66    | 0.92 | 0.80    | 0.98 | 0.94    | 0.99 | 0.99    | 1.00 | 1.00    | 1.00 |

